#### Handling of missing data and loss to follow-up

The data will be checked for missing values. If there are few participants with missing values (< 1%) for many important covariates (such as physical assessment e.g. weight and grip strength), they will be removed from the analysis of primary and secondary outcomes. If there is less than 1% of data missing then no imputation will be carried out. A sensitivity analysis will examine whether including or excluding imputation makes a difference to the result. Every effort will be made to minimise missing data. Secondary analyses (limited to the primary outcome) will be performed that involve joint modelling of missing data for sensitivity assessment. The statistical packages SAS 9.4 and IBM SPSS Statistics 25 will be used for all analyses.

*Cost-effectiveness analysis* will consider whether either or both interventions are cost effective relative to social contact (no intervention) and will (initially) report on a within-trial basis from within-a-payer (District Health Board) perspective. Costs counted include intervention costs, residential care costs, hospitalisation costs (from routinely collected New Zealand Ministry of Health data), and will be valued according to the type of hospital admission (e.g. diagnosis/speciality) and length of stay. Unit costs will be sourced where available from national level data, supplemented by information from the literature where no suitable national level source exists. Quality of life is assessed from baseline to 12 months post-intervention and will be used to estimate quality-adjusted life years (QALYs), with the value for money of the intervention assessed using incremental cost-effectiveness ratios. As the analysis is within 12 months, discounting is not required and the analysis will use 2017/18 New Zealand Dollars as its base year.

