**Methods:**

A multi-centre randomised controlled assessor-blinded study. The four intervention groups are SC, an 8-week nutrition education and cooking class; SAYGO, a 10-week strength and balance exercise class; SC plus SAYGO, and a social group (Control). Community-dwelling adults aged 75+ (60 + Māori and Pasifika) in New Zealand are recruited through health providers. Participants are not terminally ill or with advanced dementia, and have a score of 1 or 2 on the FRAIL questionnaire. Baseline assessments are completed using standardised questionnaires prior to randomisation. Four follow-up assessments are completed: immediately after intervention, 6, 12 and 24 months post-intervention. The primary outcome is frailty score, secondary outcomes are falls, physical function, quality of life, food intake, physical activity, and sustainability of the strategy. Study outcomes will be analysed using intention-to-treat approach. Cost analyses will be completed to determine if interventions are cost effective relative to the control group.

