## Methods

This trial aims to determine the effectiveness and cost-effectiveness of the SC and/or SAYGO programmes to prevent frailty in pre-frail older adults.

Design: A multi-centre randomised controlled, assessor-blinded, 2 × 2 factorial study.

Setting and characteristics of participants: Community-dwelling older adults aged 75+ (60 + Māori and Pasifika) across four sites in both the main islands of New Zealand (North and South Islands), with no upper age limit. Māori are the indigenous Polynesian people of New Zealand and Pasifika people are migrants from the South Pacific Region who are living in New Zealand. Health inequalities between the Māori/Pasifika and non-Māori/non-Pasifika are evident [26] and Māori/Pasifika people have lower life expectancy than non-Māori/Pasifika [27], so that applying uniform eligibility criteria would exclude Māori and Pasifika older people.

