### Interventions

After participants complete baseline assessments, they are randomly assigned to one of four groups: SC, SAYGO a group strength and balancing exercise, both SC and SAYGO, and social group (control group).

**Senior Chef** is a weekly 3-h session run for 8 weeks by a trained facilitator following set lesson plans. The 3-h session comprises a morning tea (or light snack) prepared by the facilitator, nutrition education, cooking together (hands-on cooking in pairs) using provided utensils and cooking facilities and then sharing the meal cooked that day. The nutrition education covers practical information about sourcing food, menu planning, budgeting and shopping tips and written information is provided to attendees to take home. After completion of the 8-week programme, the group is encouraged to continue to meet as peers as coordinated by the facilitators.

SAYGO (Steady As You Go) is a weekly 1-h session of exercises to strengthen lower limb muscles and to challenge balance for 10 weeks led by a professionally trained facilitator. The exercises are based on the Otago Exercise Programme, one proven to reduce falls and be sustainable [30]. The programme was adapted for group delivery by physiotherapists and found to be effective in improving physical function in those who participate [22]. During the first 6 weeks, potential peer leader(s) are encouraged by the professionally trained facilitator to consider being a peer leader. Other participants in the group are encouraged to support the peer-led class by helping arrange and set up the venue, collect gold coin donations and take attendance. At week 9, peer leaders are invited to take the class in their community and go through a 1-day training. The training includes a physiotherapy-developed manual and covers class safety, fall prevention, specific exercise routines and first aid workshop. There is a CD with all the exercises that peer leaders use to teach their class to maintain fidelity. The peer leaders and class members decide on the venue for the classes, and continue to meet weekly.

Social group (control) is a weekly 1–2-h “seated” (i.e. non-physical in nature) socialising group facilitated in the local community for 10 weeks. Following the 10-week period, participants are encouraged to continue to attend social groups.

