This trial is designed to be a real-world rigorous assessment to address two main questions: are nutrition and/or strength and balancing exercise programmes effective in preventing frailty in pre-frail community-dwelling older people? If yes, how cost effective are these programmes? The first question helps public health professionals to understand which strategy is better in postponing frailty and the process outcomes facilitate the understanding of the underlying changes prior to observable clinical improvements. It is also the interest of older adults to maintain function and independence in later years. The second question is a fundamental interest to payers and policy-makers. We also evaluate the sustainability of participation after the formal facilitated programmes with an opportunity to enhance the role of older people through peer-led intervention. We aim for long-term follow-up to 24 months. Recruitment to the current study began in April 2016 and the trial expects to report in 2020.

We acknowledge the importance of working in partnership with the older adults and the local communities to facilitate sustainability of the intervention programmes. Feedback will be sought from the study participants and the programme facilitators to support the transition into peer-led groups. The health approach of older Māori and Pasifika is likely to be unique. It is vital for us to work with the relevant local stakeholders to guide the adaptation of the intervention programme to ensure these are culturally appropriate and acceptable. Consultations with relevant groups and older Māori/Pasifika are carried out prior to the initiation of the trial.

If successful, this will generate valuable information about efficacy of the nutrition and exercise strategies, but also provide insightful information for implementation. We will report exactly what happened and involvement of the participants and stakeholders in this trial. Trials require replication as strategies may have different impacts in different health systems and populations, but without well-designed and rigorously conducted trial set in the real world, attempts to reduce frailty and improve outcomes for older people in our ageing societies may waste valuable resources.

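### The only cost-effectiveness comparison named is against the social group, mislabelled as no intervention, although a payer chooses among four exclusive arms

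*Protocol article*

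**What the plan says.** The economic paragraph of the protocol article, placed under Handling of missing data and loss to follow-up, says the analysis "will consider whether either or both interventions are cost effective relative to social contact (no intervention". The Methods part of the abstract puts the same question: "Cost analyses will be completed to determine if interventions are cost effective relative to the control group". The metric follows later in the economic paragraph, "with the value for money of the intervention assessed using incremental cost-effectiveness ratios", without a list of comparators. The perspective is that of a payer, within the trial, with QALYs to 12 months after the intervention.

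The design is described as "A multi-centre randomised controlled, assessor-blinded, 2 × 2 factorial study". Its four arms are Senior Chef (SC, cooking), SAYGO (exercise), SC plus SAYGO, and a social group.

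The comparator is described in two other places. Under Interventions it is a weekly "socialising group facilitated in the local community for 10 weeks", after which participants are encouraged to keep attending. The abstract counts it among the intervention groups: "The four intervention groups are SC, an 8-week nutrition education and cooking class" opens a list that ends with the social group.

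**The concern.** There are two linked problems.

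**The comparison.** A payer can fund one of four options: the social group, cooking, exercise or both. For the combination, a ratio against the social group averages the value of the first programme into that of the second. It does not by itself show whether the second programme is worth its extra cost once the better single one is in place. That needs the ratio against the next best option, and the article names no such comparison. Cost-effectiveness is half of the stated aim, and the option most exposed to a flattering ratio is the combination.

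**The label.** The economic paragraph equates social contact with no intervention. Elsewhere the article describes a facilitated programme that uses staff time and may itself affect outcomes. A reader of the published ratio would be told the wrong thing about what it is measured against.

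**Working it through.** **What can be reproduced.** The article states no cost, QALY gain, willingness-to-pay threshold or ratio, so there is no figure to reproduce. All costs, QALY gains and the threshold below are assumptions that show the mechanism; none is a prediction for this trial.

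**Formulas.** Incremental cost-effectiveness ratio (ICER) = ΔC / ΔQALY. Net monetary benefit (NMB) = λ × ΔQALY − ΔC, where λ is the threshold per QALY.

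**Illustration 1.** Assumed differences from the social group: exercise +$300 and +0.020 QALY; both programmes +$800 and +0.024 QALY.

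- Exercise against social: 300 / 0.020 = $15,000 per QALY.
- Both against social: 800 / 0.024 = $33,333 per QALY.
- Both against exercise: (800 − 300) / (0.024 − 0.020) = 500 / 0.004 = $125,000 per QALY.

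**Illustration 2: how much overlap is needed?** Assumed differences from the social group: SC +$600 and +0.015 QALY; SAYGO +$200 and +0.020 QALY; both +$800 (costs add). Assumed λ = $50,000. Let s be the share of the SC gain that is kept when SC is added to SAYGO. Both programmes then gain 0.020 + 0.015s QALY, and the ICER of both against SAYGO is 600 / (0.015s). NMB against social is 50,000 × 0.020 − 200 = $800 for SAYGO alone and 50,000 × 0.015 − 600 = $150 for SC alone.

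| s | QALY gain, both | Both vs social ($/QALY) | Both vs SAYGO ($/QALY) | NMB, both ($) | Best option |
|---|---|---|---|---|---|
| 100% | 0.03500 | 22,857 | 40,000 | 950 | Both |
| 75% | 0.03125 | 25,600 | 53,333 | 762.5 | SAYGO alone |
| 50% | 0.02750 | 29,091 | 80,000 | 575 | SAYGO alone |
| 25% | 0.02375 | 33,684 | 160,000 | 387.5 | SAYGO alone |
| 0% | 0.02000 | 40,000 | infinite | 200 | SAYGO alone |

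The combination stays below the assumed threshold against the social group in every row. Against SAYGO alone it crosses the threshold when 600 / (0.015s) = 50,000, that is at s = 0.80.

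**The additive case.** With s = 100% and additive costs, the ratio for adding SC to SAYGO (600 / 0.015 = $40,000) equals the ratio for SC alone against social. The comparisons that the article names then already contain the answer.

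**The label, side by side.** The economic paragraph says no intervention. The Interventions section describes a facilitated group that meets for one to two hours each week over ten weeks, and its provision for transport help excludes no arm. The abstract lists the group as one of four intervention groups. The first statement cannot stand beside the other two.

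**The case against.** The strongest reply is that the article never says the social group is the sole comparator. It promises incremental ratios and excludes no pair of arms. It is also a condensed article, so ranking rules, dominance and the threshold may sit in a fuller economic plan. That stands: a reader might infer that a full incremental analysis has been ruled out, and the text does not support that. What remains is that the question is posed twice, each time against the social group or control, and nothing else is named.

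Second, differences against a common control yield every other pairwise difference by subtraction, and under additivity nothing is lost. Both points are correct. They show that the remedy is cheap and the harm conditional; they do not make the stated question the right one for a choice among four options.

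Third, a reader might cite the Discussion, where the first research question "helps public health professionals to understand which strategy is better in postponing frailty", as proof that the economic analysis sets out to rank the arms. It is not: that sentence concerns effectiveness, and the economic question is put separately.

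Fourth, a reader might infer from the label that the control arm will be costed at zero. With an assumed difference of $500 and 0.02 QALY before any control cost, the ratio would be 500 / 0.02 = $25,000 per QALY. Counting $100 to $300 per control participant gives 400 / 0.02 = $20,000 to 200 / 0.02 = $10,000. But the article states no such costing rule. It counts intervention costs and lists the social group among the interventions, which points the other way. A zero-cost control would also raise every ratio, so it would work against a mistaken endorsement of the combination.

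Finally, the figures are invented. They are, and they establish only that the mechanism works.

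**Conclusion.** The concern holds in a limited form. The comparison that the article names does not by itself answer the choice a payer faces among four exclusive arms. If the programmes' effects are sub-additive, the combination can look cost effective against the social group while the second programme is poor value on top of the better single one: about $33,300 against $125,000 per QALY in the first illustration. In the second, the reversal begins once less than 80% of the SC gain is kept. Both results rest wholly on assumed costs, gains and threshold. If effects are fully additive, the problem need not occur, so the error is possible and not certain.

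The label is a plain contradiction within the article and needs no assumption. It misstates what the ratios are measured against. It does not show that the control arm's costs will be left out.

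**What to change.** - State a full incremental analysis of all four arms: rank by cost, remove dominated and extended-dominated options, and report each ICER against the next best remaining option. Add net benefit or acceptability curves for the four arms jointly.
- Keep each option against the social group as a secondary presentation.
- Delete the no-intervention label, describe the comparator as a facilitated social group, and state that its delivery costs (facilitator, venue, transport) are counted on the same basis as in the other arms.

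The cost is some extra analysis of data already being collected, plus recording what the social group costs to deliver. No further participants or visits are needed.

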Health-related quality of life will be assessed with the Short Form (SF-12) including the summary scores for physical and mental health-related QOL [41]. Individual-level responses from the SF-12 can be translated into a preference-based quality of life measuring health on a utility scale where ‘dead’ scores 0 and ‘full health’ scores 1. These repeated individual utilities can be used to construct QALYS [41] by plotting time against quality of life and identifying the area under the plotted curve. This QALY measure identifies health over a period of time and is used in the cost-effectiveness analysis.

Process outcomes will also be used as secondary outcomes, namely food intake and reduced sedentary time. Food intake will be assessed using the INTAKE24, an online dietary tool developed by a team in Newcastle University, Newcastle upon Tyne, UK [42]. INTAKE24 is based on the 24-h multiple-pass recalls (MPR) dietary assessment with the New Zealand FOODfiles 2016 database incorporated into the programme. The MPR protocol is suitable for use in the general [43] and oldest old population and matches that used in the Newcastle 85+ and LiLACS NZ studies [44, 45]. Two 24-h MPR will be completed on two separate days (a weekday and a weekend) by a trained interviewer at the participants’ residence or a venue suitable for them.

Physical activity will be determined using the CHAMPS Activities Questionnaire. CHAMPS is a validated questionnaire to measure sedentary (1 METs), low-light (> 1 and ≤ 2 METs), high-light (> 2 and < 3 METs), moderate-to-vigorous physical activity (MVPA, ≥ 3 METs), and total activity in older people over a 4-week period [34, 35].

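### The QALY period (baseline to 12 months after the programme) cannot lie within 12 months, and read literally it is two weeks shorter for Senior Chef than for control

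*Protocol article*

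**What the plan says.** The cost-effectiveness paragraph, under Handling of missing data and loss to follow-up, states the period over which utilities are gathered: "Quality of life is assessed from baseline to 12 months post-intervention". It then explains why discounting is omitted: "As the analysis is within 12 months, discounting is not required". Under Outcome measures, QALYs are built from repeated SF-12 utilities "by plotting time against quality of life and identifying the area under the plotted curve".

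The visit clock is given in the Abstract: "Baseline assessments are completed using standardised questionnaires prior to randomisation", and "Four follow-up assessments are completed: immediately after intervention, 6, 12 and 24 months post-intervention". Table 1 and the section on data collection give the same schedule, with month 0 at the end of the programme.

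Under Interventions, Senior Chef "is a weekly 3-h session run for 8 weeks by a trained facilitator following set lesson plans", while SAYGO "is a weekly 1-h session of exercises to strengthen lower limb muscles and to challenge balance for 10 weeks". The social control group also runs for 10 weeks. No length is given for the arm that receives both programmes. Cost-effectiveness is judged against the social group.

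**The concern.** The two statements in the cost-effectiveness paragraph do not fit together. A period that starts before the programme and ends 12 months after it is longer than 12 months by at least the length of the programme. The reason given for not discounting is therefore not true of the period described.

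The second problem follows from the same sentence. An area under a utility curve increases with the time it covers. If the end point is fixed relative to the end of each arm's own programme, an arm with a shorter programme is integrated over less time and collects fewer QALYs even when health is identical. Senior Chef is two weeks shorter than its comparator. The incremental QALY for that comparison would then contain a component that comes only from the schedule. Cost-effectiveness is a stated aim of the trial alongside effectiveness, so the horizon should be unambiguous.

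**Working it through.** **Inputs from the article**
- Programme length: Senior Chef 8 weeks; SAYGO 10 weeks; social control 10 weeks; combined arm not stated (Interventions).
- Start of the period: baseline, before randomisation. End of the period: 12 months after the programme.
- QALY = area under the utility-time curve.

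**Assumptions, because the article gives no figure**
- Mean utility 0.7, range 0.6 to 0.8, flat over time and equal in all arms (no treatment effect).
- No wait between baseline and the first session, which gives the shortest possible period.
- Discount rate 3% to 5%.
- One week = 7/365.25 year.

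**Step 1. Can the stated 12 months be reproduced?**
Period = programme length + 12 months.
- Senior Chef: 8 + 52 = about 60 weeks; 1 + 8 × 7/365.25 = 1.153 years = 13.8 months.
- SAYGO and control: 10 + 52 = about 62 weeks; 1 + 10 × 7/365.25 = 1.192 years = 14.3 months.

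Neither is 12 months or less. An assumed 4-week wait before the first session would give 14.8 and 15.2 months. Two other choices would give 12 months: starting at the end of the programme, which contradicts the stated start at baseline, or cutting the curve 12 months after baseline, which the article does not state.

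**Step 2. Difference between arms with no treatment effect**
Senior Chef versus control: 10 − 8 = 2 weeks = 0.0383 year.

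| Assumed utility | Utility × 0.0383 | Spurious QALY deficit for Senior Chef |
|---|---|---|
| 0.6 | 0.6 × 0.0383 | 0.023 |
| 0.7 | 0.7 × 0.0383 | 0.027 |
| 0.8 | 0.8 × 0.0383 | 0.031 |

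To offset this at utility 0.7, Senior Chef would need a true utility gain of 0.7 × 0.0383 / 1.153 = 0.023, sustained over the whole period.

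SAYGO versus control: 10 − 10 = 0 weeks, so no stated gap. Combined arm versus control: 0 weeks if the two programmes run concurrently over 10 weeks; otherwise unknown.

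**Step 3. Size of the discounting error**
With x the time beyond one year and r the rate, the proportionate loss in total QALYs is x(1 − 1/(1 + r)) / (1 + x).
- Smallest: x = 0.153 (8 weeks), r = 3%: 0.4%.
- Largest: x = 0.192 (10 weeks), r = 5%: 0.8%.

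This is a fraction of the total. Its effect on a difference between arms is smaller still in absolute terms.

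**Step 4. Does a 52-week window work with the planned visits?**
The 6-month visit falls at about week 8 + 26 = 34 or 10 + 26 = 36, and the 12-month visit at about week 60 or 62. Week 52 lies between them, and SF-12 is collected at both (Table 1). With a flat utility of 0.7, each arm then has 0.7 × 1 year = 0.70 QALY and the spurious difference is zero.

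**The case against.** The strongest reply is that the first statement describes data collection and the second describes the analysis. Utilities gathered up to the 12-month visit could be integrated over a common 12 months from baseline, and then nothing is wrong. That reading is possible and is close to the fix below, but the article does not state it. It names only one period in connection with QALYs, and a reader who follows it would integrate over that period.

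A second reply is that visits may follow a common calendar. Table 1 shows one schedule for all four groups, and visits two weeks earlier in one arm could hint at allocation to blinded assessors. If so, the two-week gap disappears. This stands as a condition on the size, not as a refutation: the text times visits from the end of the intervention and mentions no common clock. Even on a common calendar the period would still exceed 12 months.

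A third reply is that integration limits and cut-off dates belong in a full protocol or an economic analysis plan. Their absence from an article is indeed no defect. The point here is that two statements which do appear conflict.

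A reader might also infer several stronger things that the document does not support:
- That every arm has a different window. SAYGO and control are both 10 weeks.
- That the combined arm gains QALYs from a longer window. That needs its programmes to run one after the other, which is not stated; run concurrently, the gain is zero.
- That costs are biased in the same way. The period for counting costs is not given.
- That the sign of the cost-effectiveness ratio would change. The article gives no expected increment against which to judge this.
- That the falls analysis shares the fault. Falls are already analysed as a rate per person-year.

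**Conclusion.** The inconsistency is real: the stated QALY period is at least 13.8 months for Senior Chef and 14.3 months for SAYGO and control, so it cannot also be the 12-month analysis that needs no discounting. As a discounting error it is negligible, at under 1% of total QALYs for assumed rates of 3% to 5%.

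The part with practical weight is conditional. If visits are timed from each arm's own end of programme and the curve is integrated over the stated period, Senior Chef carries a spurious deficit of about 0.027 QALY against control (0.023 to 0.031). This rests on the assumed utilities of 0.6 to 0.8, flat and equal between arms. It concerns the Senior Chef comparison only, and the primary frailty result is untouched.

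**What to change.** Define one horizon, counted from randomisation, for both QALYs and costs in all four arms. One option is 0 to 52 weeks, with the baseline SF-12 as the starting value, linear interpolation to week 52 between the 6- and 12-month post-intervention SF-12 visits, and costs cut at the same date. The no-discounting statement is then true as written. The alternative is to state a longer common horizon from randomisation together with its discounting rule.

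The cost is a change of wording and slightly more analysis work. No visit is added or moved, SF-12 is already collected at every time point, and hospitalisation costs come from routinely collected national data, which should allow a cut at a fixed date. With the 52-week option, utilities measured after week 52 serve only for interpolation. The falls analysis needs no change.
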